# Comparing the efficacy of a web-assisted calprotectin-based treatment algorithm (IBD-live) with usual practices in teenagers with inflammatory bowel disease: study protocol for a randomized controlled trial

**DOI:** 10.1186/s13063-015-0787-x

**Published:** 2015-06-16

**Keywords:** Children, Inflammatory bowel disease, Crohn’s disease, Ulcerative colitis, Self-monitoring, Calprotectin, Telemedicine, E-health

## Abstract

**Background:**

To prevent clinical relapse in teenagers with inflammatory bowel disease (IBD) there is a need to monitor disease activity continuously. Timely optimisation of medical treatment may nip a preclinical relapse in the bud and change the natural course of IBD. Traditionally, disease monitoring is done during scheduled visits, but this is when most teenagers report full control. IBD care could be more efficient if patients were seen at times of clinical need. This study aims to examine the effectiveness of a web-assisted calprotectin-based treatment algorithm (IBD-live) compared with usual practices in teenagers with IBD.

**Methods/design:**

A randomized trial of web-based disease monitoring versus usual care is conducted at 10 Dutch IBD care centers. We plan to recruit 180 patients between 10- and 19-years old with quiescent IBD at baseline. Teenagers assigned to IBD-live will use the flarometer -an automatic cumulation of disease activity and fecal calprotectin measurements- to estimate probability of relapse. In case the flarometer indicates high risk the patient requires treatment intensification in accordance with national guidelines; low risk means that maintenance therapy is unchanged; and intermediate risk requires optimisation of drug adherence. Patients assigned to usual practice get the best accepted medical care with regular health checks. Primary outcome is the frequency of relapse at 52 weeks of follow-up. The diagnosis of relapse is based on a clinical activity index score >10 points necessitating remission induction therapy. Secondary outcomes include quality of life and cost-effectiveness.

**Discussion:**

Web-assisted monitoring of disease activity with rapid access for those with acute relapse may allow teenagers to develop skills that are required of adult patients (including communication and self-determination). Similar monitoring systems have been introduced for teenagers with asthma and diabetes, with a positive effect on disease control, but the intervention has not been evaluated in teenagers with IBD. A randomized trial in adult patients with ulcerative colitis showed that a web-assisted treatment algorithm is feasible, safe and cost-effective. Results of the current trial are expected to have important implications for teenagers with IBD that incurs substantial health burdens and economic costs.

**Trial registration:**

Dutch Trial Register identifier: NTR3759 (registered 29 December 2012)

## Background

Inflammatory bowel diseae (IBD) includes two major forms of intestinal inflammation: Crohn’s disease and ulcerative colitis. In both types inflammation waxes and wanes over time in an unpredictable fashion. Treatment of children and adolescents with IBD is aimed at inducing and maintaining remission of disease activity to ensure normal growth and pubertal development, and improving the quality of life of patients. To prevent relapses there is need for continuous monitoring of disease activity for timely optimisation of medical treatment.

Twenty five per cent of the total IBD cases present in childhood or adolescence [1], and the incidence is increasing [2–4]. In the Netherlands each year approximately 250 teenagers are diagnosed with IBD [5]. Health professionals confronted with the increased disease burden may be interested in finding ways to ease the pressure on overstretched clinics with new approaches to monitor disease activity in IBD.

### Existing knowledge

Endoscopy is the standard for assessing intestinal inflammation [6], but the invasive nature of the procedure limits its use for routine evaluation of disease activity. Intensification of treatment in teenagers is therefore guided by regular use of clinical composite scores including the Pediatric Crohn’s Disease Activity Index (PCDAI) [7] and the Pediatric Ulcerative Colitis Activity Index (PUCAI) [8]. When used as stand-alone tests these scores may be subject to bias. High scores may reflect relapse, but could also be caused by gastrointestinal symptoms not related to IBD, such as irritable bowel syndrome. Moreover, underreporting the symptom burden is a characteristic coping strategy for teenagers during a face-to-face conversation with a physician [9]. Traditionally, many clinicians use C-reactive protein (CRP) as an objective add-on test to monitor disease activity [10].

Fecal calprotectin (fCal) is a noninvasive marker of inflammation that correlates well with endoscopic and histopathological disease activity [11]. Measuring fCal is a useful screening tool for identifying patients who are most likely to need endoscopy for suspected IBD [12]. We assessed the value of periodic CRP and fCal testing to predict early relapse in teenagers with confirmed IBD [13]. We followed 62 patients who claimed to have no symptoms and found that fCal levels increase prior to CRP and before manifestations of clinical symptoms. The positive predictive value to detect early relapse was 40 % with CRP and 60 % with fCal testing. We concluded that fCal is a better add-on test to monitor disease activity than CRP. Periodic use of fCal could help to identify teenagers who require treatment intensification at the time of minimal disease rather than at the time of clinically overt relapse.

### Home monitoring of disease activity and treatment algorithm

The above described “Full Control Study” [13] provided evidence that disease activity scores and fCal measurements are the best combination to predict relapse in teenagers who are doing well. Building on this we designed a relapse risk stratification tool (flarometer, Figure 1) that can be used at home. The flarometer is an automatic cumulation of patients’ answers to disease activity questionnaires (PUCAI or the short version of the PCDAI (shPCDAI) [14], which excludes blood test results). After completion of these questionnaires the web application asks the patient to send a stool sample to the Department of Laboratory Medicine of the University Medical Centre Groningen, where it is analysed for fCal with a rapid test. In case the PUCAI or shPCDAI indicates moderate to severe disease activity, the patient is automatically advised not to await the stool result, but to immediately contact the local IBD-team. The stool result is entered into the flarometer system within 24 hours after reception, and a customized clinical alert is transmitted to the patient and local IBD-team. The advice will vary with the position of the pointer on the flarometer scale. When the pointer is in the high-risk stratum, clinical relapse is highly suspected and the local IBD-team is advised to intensify treatment in accordance with national guidelines [15]. In the low-risk stratum maintenance therapy remains unchanged and an alert to use the flarometer will be sent in three months. In the intermediate range, drug adherence is optimised and the flarometer will be used again in a month. After two consecutive intermediate results the local IBD-team is advised to intensify treatment (Fig. 2).

**Fig. 1 Fig1:**
[figure not shown]
Flarometer home monitoring strategy and treatment algorithm

**Fig. 2 Fig2:**
[figure not shown]
Graphical representation of flarometer test frequency and treatment advice. In the high-risk stratum, clinical relapse is suspected and the local IBD-team is advised to intensify treatment and remeasure in one month. In the low-risk stratum, maintenance therapy remains unchanged and an alert to use the flarometer will be sent in three months. In the intermediate range, drug adherence is optimised and the flarometer will be used again in a month. After two consecutive intermediate results the local IBD-team is advised to intensify treatment. This scenario is shown at eight months. *IBD* Inflammatory bowel disease

### Need for a trial

Web-assisted monitoring of disease activity with rapid access for those with acute relapse may allow teenagers to develop skills that are required of adult patients (including communication and self-determination) [16]. A randomized trial in adult patients with ulcerative colitis showed that a web-assisted treatment algorithm is feasible, safe and cost-effective compared to usual care. The intervention increased compliance and quality of life, and reduced healthcare costs [17]. Web-based disease monitoring has been introduced for teenagers with asthma [18] and diabetes [19], with a positive effect on disease control, but the intervention has not been evaluated in teenagers with IBD.

The trial described in this protocol aims to examine the efficacy of a web-assisted calprotectin-based treatment algorithm, compared with usual practice, on disease course among teenagers with IBD. This project will move IBD care for teenagers into a new era, from traditional paternalism (the doctor at the wheel) to a phase in which teenagers take ownership of their chronic disease and participate in the therapeutic decision-making process (teenagers at the wheel). Informing teenagers periodically about fCal results may enable them to understand better the importance of adherence. Studies in adults report that 30–45 % of patients do not use maintenance drugs regularly [20], and nonadherence among teenagers is even higher [21]. Nonadherent patients have an increased risk of clinical relapse [22] and generate greater annual health care costs than adherent patients [23]. Furthermore, the IBD-team could be used more efficiently if patients were seen at times of clinical need, instead of during three-monthly routine visits.

### Choice of comparator

Treatment in the group assigned to usual practices represents the currently best-accepted IBD care. For teenagers with IBD in remission this means regular checks at the outpatient clinic as before the trial. A health check includes a physicians’ rating of disease activity and blood sampling. In case of clinical relapse the patient is advised to intensify treatment in accordance with national guidelines [15]. When a patient experiences a relapse between two regular health checks, rapid access to specialist care is provided.

### Study objectives

We aim to compare the effect of treatment delivered according to a web-assisted calprotectin-based algorithm (IBD-live) against the same treatment delivered according to usual practice.

We hypothesize that use of IBD-live may reduce the relapse rate during a 52-week follow-up period. Furthermore, we postulate that users of IBD-live have higher scores on the disease specific quality of life IMPACT-III questionnaire, and that use of IBD-live is accompanied by lower costs of disease management as compared to usual care.

### Trial design

This trial is designed as a randomized, controlled, open label multicenter superiority strategy trial with two parallel groups. For allocation concealment, randomization will be carried out using a separate list of computer-generated random allocation numbers for each participating center (involving permuted blocks with a ratio of 1:1 allocation).

## Methods—participants, interventions, and outcomes

### Study setting

Study participants will be recruited from six tertiary care centers in the Netherlands (Groningen, Amsterdam (2x), Rotterdam, Utrecht and Leiden), and from four large general teaching hospitals (The Hague, Zwolle, Enschede and Arnhem). The principal investigators at the various sites are members of the Kids with Crohn’s and Colitis (KiCC) working group for Collaborative Research in the Netherlands. Together they treat about two-thirds of the total pediatric IBD population in the Netherlands.

Since 2007 national treatment guidelines for IBD are in use that have provided uniformity in treatment [15]. Immunomodulation with thiopurines is the first choice in patients with Crohn’s disease. In case of failure or intolerance methotrexate can be used. In ulcerative colitis the first choice is aminosalicylate monotherapy. Thiopurine co-medication is recommended in those with frequently relapsing disease. Teenagers with active Crohn’s are treated with steroids and gradual dose tapering, or with an exclusive oral polymeric diet for six weeks. Patients with active ulcerative colitis are treated with steroids and aminosalicylate dose escalation. Anti-tumor necrosis factor (TNF) antibodies are labeled for use after failure of conventional therapy (step-up).

### Inclusion and exclusion criteria for participants

Approximately 10 % of teenagers with IBD will have a severe disease course and require use of the complete arsenal of available therapies in a limited period of time to maintain remission. We aim to include the other 90 % of teenagers with a more stable disease course.

Eligible patients are those: 10- to 19-years old, with quiescent IBD for more than three months before study enrollment, with IBD diagnosed according to the Porto criteria [24] more than six months before enrollment, who have access to internet, with knowledge of the Dutch language, and with an adult caregiver who is willing to actively support participation.

Potential participants will be excluded from the study if any of the following conditions occur: maintenance treatment with infliximab or adalimumab (for unavoidable frequent contact with health providers); presence of ileostomy or ileoanal pouch (as fCal cut-off is not validated for small bowel feces); or any comorbidity at the time of enrollment that requires hospitalization or frequent blood sampling.

### Interventions

Teenagers assigned to the experimental arm of the trial have access to all modules of the web-based portal: (1) the flarometer, an automatic cumulation of an online patient rated PUCAI or shPCDAI, and the result of a fCal point of care test (Quantum Blue® Calprotectin, Bühlmann Laboratories AG, Schönenbuch, Switzerland); (2) a module for direct communication with the local IBD team with guaranteed feedback within two working days; and (3) a module with study questionnaires (quality of life, drug adherence, absenteeism and health care utilization). They will have six monthly health checks at the outpatient clinic to monitor potential adverse effects of the medication. In between these visits teenagers receive alerts to use the flarometer.

The frequency of use depends on the previous flarometer score (Figure 1). When the score is in the high (red) or moderate (orange) risk stratum, next flarometer use is advised after one month. In the low (green) risk stratum an alert to use the flarometer will be sent in three months. Teenagers have the freedom to use the flarometer more often, but fecal samples can only be sent once a month. In case the flarometer is not used despite three reminders (text or e-mail message), the IBD-nurse will contact the teenager by phone.

Both teenager and local IBD team will receive a computer-generated e-mail with the flarometer result, which also includes treatment advice. In the high (red) risk stratum the teenager is advised to contact the local IBD-team for treatment intensification. In case the teenager fails to contact the IBD-team, the IBD-nurse will instead call the teenager. In the low (green) risk stratum maintenance therapy remains unchanged. The intermediate (orange) risk stratum requires evaluation of an imminent relapse, drug adherence and potential intercurrent gastrointestinal infections.

The local IBD-team has the freedom to ignore the flarometer treatment advice, but this should be well-founded and indicated in the patient file. The web-assisted algorithm is certainly not meant to replace the pediatrician. It is intended to guide both pediatricians and patients in joint decisions whether or not to intensify treatment by providing more objective estimates of probability, as a supplement to other relevant clinical information. Any therapeutic intervention remains the responsibility of the treating pediatric gastroenterologist.

### Interventions—modifications

Study participants from both groups are instructed to contact their doctor immediately to report clinical deterioration between regular health checks, or if at any time they want a consultation (side effects, other health related questions). Rapid access to specialist care is guaranteed for both groups. All unscheduled health visits (including those at the IBD clinic, general physician and emergency department) and hospital admissions are documented in the study data tracking system and are reported as adverse events. Crosschecking will be done by comparing doctor reported health consumption and patient-reported health consumption.

Study participants can leave the study at any time for any reason if they wish to do so without any consequences. The local principal investigator can decide to withdraw a teenager from the study for urgent medical reasons. Another patient from the same center may then be randomized to enter the study.

Patients withdrawn from the experimental arm of the trial will continue with usual care, outside the scope of this study, as would have happened otherwise. Patients who receive usual care and withdraw from the study will continue to receive usual care as before entering the study.

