### Retention

Once a teenager is randomized, the study site will make every reasonable effort to follow the patient for the entire study period of 52 weeks. It is projected that the rate of loss-to-follow-up will be at most 10 %. Retention will be promoted by sending automated reminders to the participants in the experimental study arm to use the flarometer, careful planning of outpatient appointments to avoid school calendar breaks, and facilitating stool collection with feces collection papers. Questionnaires will be completed digitally via a hyperlink sent by email, which will further limit participant burden.

There will be no explicit incentive for study participants. Participation in a child friendly website may be perceived as an incentive, but it is not an incentive in a material sense. Teenagers in the experimental arm will have access to the website, while the controls will only have access to the study questionnaires.

A participant who withdraws consent for follow-up assessment of any of the secondary outcomes will be given the option to continue with assessments for the primary outcome.

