### Statistical methods

The statistical analysis will be coordinated by a statistician from the biostatistics unit of the UMCG. The primary analyses will be conducted using an intention-to-treat basis. All teenagers recruited into the study will be included in these analyses; patients will be analyzed within the group (IBD-live or usual practice) to which they were randomized irrespective of what care they actually received. Where appropriate, secondary analyses will be conducted using a per protocol basis. These analyses will be restricted to just those teenagers who replied to more than 80 % of the alerts to use the flarometer and to the teenagers in the control group who replied to more than 80 % of the requests to send a stool sample for fCal measurement.

As earlier published web-based programs have focussed on patients with ulcerative colitis [17, 35, 36], we made an a priori decision to do a subgroup analysis to examine the intervention in two subtypes of IBD (ulcerative colitis and Crohn’s disease). We will use a test of interaction to examine whether the treatment effect differs between these subgroups. In case of random missing data multiple imputation will be performed using the hot deck method [37].

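### Investigator withdrawal ends study participation with no stated outcome follow-up, so relapses can be lost in a way that depends on prognosis

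*Protocol article*

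**What the plan says.** Protocol article, Interventions—modifications: "The local principal investigator can decide to withdraw a teenager from the study for urgent medical reasons". The reasons are not defined further. The next sentence is "Another patient from the same center may then be randomized to enter the study". For the experimental arm the section continues: "Patients withdrawn from the experimental arm of the trial will continue with usual care, outside the scope of this study". For usual practice it says only that a patient who withdraws keeps the same care as before.

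Protocol article, Retention: from allocation onwards, "the study site will make every reasonable effort to follow the patient for the entire study period of 52 weeks". One route for keeping the primary outcome is described: "A participant who withdraws consent for follow-up assessment of any of the secondary outcomes will be given the option to continue with assessments", meaning those of that outcome.

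Protocol article, Statistical methods: "All teenagers recruited into the study will be included in these analyses", and "patients will be analyzed within the group (IBD-live or usual practice) to which they were randomized irrespective of what care they actually received". On missing data: "In case of random missing data multiple imputation will be performed using the hot deck method".

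Protocol article, Outcomes and Sample size: time to relapse is compared by Kaplan-Meier curves, a log-rank test and Cox regression. The target is a 15-point absolute reduction at 52 weeks with 90 patients per group, a number that already allows for up to 10% loss to follow-up. Participants, care providers and outcome assessors are not blinded (Randomization and masking).

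**The concern.** This is a strategy trial. Moving from IBD-live back to usual care is exactly the kind of departure that analysis by assigned group is meant to absorb. The withdrawal rule instead treats it as leaving the study. The exit is triggered by a medical reason and decided by someone who knows the allocation, and the article gives no route for learning afterwards whether the patient relapsed.

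The endpoint has two parts, an activity score above 10 points and a need for one of the listed induction treatments. A patient could therefore be withdrawn while worsening but before both parts are on record. A survival analysis would by default censor that patient at withdrawal and treat the remaining patients in the arm as representative of the one who left. If withdrawals of this kind differ between the arms, the comparison of relapse is biased.

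**Working it through.** **Setting the passages side by side**

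1. Retention commits sites to a reasonable effort to follow every randomized patient for 52 weeks. Interventions—modifications puts a patient withdrawn from IBD-live outside the study. The commitment is not absolute, so this is tension and not a flat contradiction.
2. Retention's option to continue primary-outcome assessment is tied to withdrawal of consent for secondary outcomes. Withdrawal by an investigator is a different event and is not covered.
3. Statistical methods keeps all recruited patients in their assigned groups. It does not say what outcome data a withdrawn patient contributes after withdrawal. Its imputation applies to random missingness, which is hard to assume when the reason for leaving is medical.

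**The plan's own figures**

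The article gives no withdrawal rate, so the shares below are assumptions. The risks of 40% and 25% come from the superseded binary calculation in Sample size. They reproduce its 152 per group: [1.960 × √(2 × 0.325 × 0.675) + 0.842 × √(0.40 × 0.60 + 0.25 × 0.75)]² / 0.15² = 151.9, rounded up to 152. The current 90 per group does not follow from 40% against 25% (Schoenfeld: 96 events / 0.325 = 296 patients, or 148 per group before loss). That is a separate matter. Here 90 serves only as a denominator.

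**Worst case in counts**

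Assume no true effect and 36 relapses among 90, or 40%. Four patients in one arm are withdrawn at a flare and none of the four flares is recorded.

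- All four leave very early: (36 − 4)/(90 − 4) = 32/86 = 37.2%.
- All four leave very late: 32/90 = 35.6%.
- The Kaplan-Meier estimate lies between these.

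The spurious difference is 2.8 to 4.4 points, or 2.79/15 = 19% to 4.44/15 = 30% of the target.

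**Range**

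Let p be the true risk, w the share withdrawn and q the share of those who would have relapsed uncounted. With early removal, the observed risk is (p − wq)/(1 − w). The implied hazard ratio is ln(1 − experimental risk)/ln(1 − control risk).

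| True risk, control / IBD-live | Withdrawn, control / IBD-live | q | Observed, control / IBD-live | Difference (points) | HR |
|---|---|---|---|---|---|
| 40% / 40% | 0 / 5% | 0.5 | 40.0% / 39.5% | 0.5 | 0.98 |
| 40% / 40% | 0 / 5% | 1 | 40.0% / 36.8% | 3.2 | 0.90 |
| 40% / 40% | 0 / 10% | 0.5 | 40.0% / 38.9% | 1.1 | 0.96 |
| 40% / 40% | 0 / 10% | 1 | 40.0% / 33.3% | 6.7 | 0.79 |
| 40% / 25% | none | – | 40.0% / 25.0% | 15.0 | 0.56 |
| 40% / 25% | 0 / 5% | 1 | 40.0% / 21.1% | 18.9 | 0.46 |
| 40% / 25% | 10% / 5% | 1 | 33.3% / 21.1% | 12.3 | 0.58 |

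For example, (0.40 − 0.05)/0.95 = 0.368. Later withdrawal shifts the risk further for the same share: 0.40 − 0.05 = 0.35. The last row shows the bias running against IBD-live. If every relapse is recorded before withdrawal, there is no shift.

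**Replacement**

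Ten per cent of 90 is 9 per group, or 18 in total. Replacing that many would randomize 180 + 18 = 198 and compensate twice for the same loss.

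**The case against.** The strongest reply is that nothing says withdrawn patients are dropped from the analysis. Statistical methods includes everyone recruited, and a withdrawn patient can stay in and contribute time up to withdrawal. That stands. A reader might infer that the withdrawal and replacement rules break intention to treat; the text does not support this. The newly enrolled patient is also randomized with concealed allocation and is not placed in the vacated arm. Replacement therefore causes no selection bias as long as the withdrawn patient is also analysed.

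A reader might also infer that the rule mainly removes relapsing patients. The documents do not say so. Relapse is the endpoint, not a stated reason for withdrawal. Both groups have rapid access to care, and relapse management is described as the same in both. A relapse that met the definition before withdrawal counts as an event. Unscheduled visits and admissions are also documented and cross-checked. The withdrawal rule applies to either arm, so the 4-patient example is one-sided by construction. The 10% allowance is for loss from any cause and does not estimate withdrawals at a flare.

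Finally, an article may leave the handling of withdrawn patients to the full protocol or analysis plan. That would answer a complaint about silence. Here, however, the article states a rule: exit is from the study, and for IBD-live the later care lies outside it. The only route it states for keeping the primary outcome does not reach these patients.

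**Conclusion.** The point holds as a weakness in a stated rule. An exit that may depend on prognosis, decided with allocation known, comes with no stated relapse follow-up. This undermines the 52-week commitment and the analysis as randomized without formally contradicting either.

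Its size is unknown because no withdrawal rate is given. Four uncounted relapsers among 90, all in one arm, would move 40% to about 36 to 37%. With no true effect, one-sided withdrawal of 5% from IBD-live gives an apparent hazard ratio of 0.98 to 0.90, and 10% gives 0.96 to 0.79, as between half and all of those withdrawn would have relapsed uncounted. These figures assume early removal and unrecorded relapses. The direction depends on which arm loses more such patients, and the bias disappears where relapse was recorded first. The point is worth correcting because the remedy is cheap; it is not evidence that the trial's result would be wrong.

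**What to change.** Amend Interventions—modifications, Retention and Statistical methods so that they agree:

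- Withdrawal by the investigator, or stopping the flarometer, ends the assigned strategy but not follow-up.
- Relapse status (activity score, induction treatment and dates) is collected to week 52 from treating-site records, unless consent for this is withdrawn.
- Every randomized patient stays in the primary analysis in the assigned group.
- Any newly randomized patient is additional and does not substitute for the withdrawn one. Alternatively, delete that sentence, since 90 per group already allows for 10% loss.
- A sensitivity analysis, applied to both arms, counts investigator withdrawals for worsening IBD as relapses.

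The cost is amendment wording and a few chart reviews. If the replacement sentence is deleted, the number of patients with complete follow-up may be slightly below 180. The clinical criteria for withdrawal are for the sponsor to reconcile; none is proposed here.
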